## Statistical analysis

3

### Possible difference between participants and drop-outs

3.1

Clinical experience in this patient population shows us that drop-out during treatment is rare. To be able to compensate for possible drop-out during the study (if needed), we aim to include 100 participants as a safety measure. A drop-out analysis on the drop-out population will be conducted: it will be studied whether there are possible differences in variables (such as: gender, age, socio-economic status, bilingualism, severity of selective mutism at baseline assessment and parental psychopathology) between the population that participates until the end of their treatment and the population that drops out. In this way it can be checked whether there is a selective dropout. A selective dropout can lead to selection bias, which could be statistically adjusted for.

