### Patient recruitment and procedure

2.1

Parents of eligible patients will be personally informed about the research project by the psychologist-researcher and will receive written information about the research project. Written informed consent will be obtained from parents/guardians for patients under the age of 12. From the age of 12 written consent will also be obtained from them. Only patients (≥12 years), who have given informed consent, or whose parents have signed informed consent will participate in this study.

After informed consent is provided, children are randomly assigned to treatment for selective mutism (N = 38) or the waiting list control group (WCG: N = 38).

Randomization will be stratified for gender, age (children aged until 7 years old are stratified into the “young” group, and children ages 8 and up are in the “old” group) and bilingualism (speaking one language, i.e. Dutch, versus speaking multiple languages). Randomization will be performed by an independent researcher, who will inform the therapists regarding the randomization outcome.

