*Sample size calculation*

A preliminary randomized clinical trial into behavioral treatment of selective mutism showed an effect size of Cohen's d = 0.58 on speaking in social situations [15]. To determine effects on our primary outcome (i.e. the pre versus post treatment change (T1-T3) on selective mutism symptoms), based on an effect size of d = 0.58 (medium effect size), an alpha of 0.05 (two-tailed) and a power of 0.8, a sample size of 76 (38 per group) is needed [30].

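### The drop-out check ignores allocated arm and has little power when drop-out is rare, so a null result cannot show that drop-out is harmless

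*Protocol article*

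**What the plan says.** Section 3.1 (Possible difference between participants and drop-outs) starts from the expectation that "drop-out during treatment is rare". It gives no rate, but raises the recruitment target to 100 as a precaution. It then plans one comparison of baseline variables "between the population that participates until the end of their treatment and the population that drops out". The variables are given as examples: gender, age, socio-economic status, bilingualism, baseline severity of selective mutism and parental psychopathology. Allocated arm is not named, either as a variable or as a way of splitting the comparison. The section concludes "In this way it can be checked whether there is a selective dropout", and adds that bias from selective drop-out could be adjusted for.

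Three other places bear on this:
- Section 2.1 randomises children 38 to 38, stratified by gender, age group and bilingualism.
- Section 2.3 places T2 at 12 weeks, when one arm has been treated and the other has waited, and T3 after the last treatment session. It says both groups receive the treatment protocol.
- Section 3.2 states intention to treat and a factorial repeated measures ANOVA of pre-post change in treatment versus waiting list.

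**The concern.** The trial's main question is a comparison between randomised arms. Drop-out threatens that comparison chiefly when the kind of child who leaves differs between the arms. A completer versus drop-out comparison over both arms together answers another question: whether those who leave differ on average from those who stay. If one arm loses its more severe cases and the other its milder ones, the average difference can be zero while the remaining arms are no longer alike.

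Such a difference is conceivable here, because for the first 12 weeks one arm is treated and the other waits. The article's reassurance concerns drop-out during treatment and does not mention leaving during the wait.

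The check also rests on a group that the article expects to be small. A non-significant result would then be likely whether or not drop-out is selective. Read as evidence that there is no problem, it could lead to an analysis without adjustment.

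**Working it through.** **Inputs.** From the article: 38 per arm, 76 in total (sections 2.1 and Sample size calculation); target 100 (section 3.1); drop-out expected to be rare, no rate given. Assumed, because the article does not state them: a two-sided t-test at 0.05 for the drop-out check, a 0.5 SD difference in baseline severity, and drop-out counts from 4 of 76 up to 24 of 100.

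**The plan's own figures.** The gap between 100 and 76 allows for 1 − 76/100 = 24% loss, and 76/(1 − 0.24) = 100. The figure of 76 itself is not reproduced from its stated inputs: d = 0.58 with "an alpha of 0.05 (two-tailed) and a power of 0.8" gives 47 per group (normal approximation) or 48 (t-test), while 38 fits a one-sided test. That is a separate matter. Here 76 and 100 serve only as group sizes.

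**Step 1: power of the planned check.** For k drop-outs and N − k completers, the noncentrality is d / √(1/k + 1/(N − k)) with N − 2 degrees of freedom. With d = 0.5:

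| Drop-outs | Noncentrality | Power |
|---|---|---|
| 4 of 76 | 0.5/√(1/4 + 1/72) = 0.97 | 16% |
| 6 of 76 | 0.5/√(1/6 + 1/70) = 1.18 | 21% |
| 8 of 76 | 0.5/√(1/8 + 1/68) = 1.34 | 26% |
| 24 of 100 | 0.5/√(1/24 + 1/76) = 2.14 | 56% |

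With 6 drop-outs of 76, a difference of about 1.2 SD is needed for 80% power.

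**Step 2: cancellation.** In 10,000 simulated trials with N = 100, drop-outs were split evenly between arms, 0.8 SD more severe in one arm and 0.8 SD less severe in the other. The pooled check was significant in 4.1% of trials with 10 drop-outs and 3.6% with 24, no better than chance. A test of whether the drop-out difference varies by arm was significant in 67% and 92%. More drop-outs do not rescue the pooled check against this pattern.

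**Step 3: splitting by arm does not cure low power.** Take opposite 0.5 SD differences with 2 drop-outs and 36 completers in each arm. The between-arm contrast is 1.0 SD with standard error √(2 × (1/2 + 1/36)) = 1.03 SD, so the noncentrality is again 0.97 and power again 16%. The split shows the right pattern, but a null result still proves little.

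**Step 4: size of the imbalance.** If a fraction q of each arm drops out, and drop-outs lie 0.5 SD above the arm mean in one arm and 0.5 SD below it in the other, each retained mean moves by 0.5q/(1 − q), in opposite directions. The retained arms then differ by 2 × 0.5q/(1 − q):
- 4 of 76 (q = 0.053): 0.056 SD
- q = 0.10: 0.11 SD
- q = 0.24: 0.32 SD

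For scale, the chance standard error of a baseline difference at 38 per arm is √(2/38) = 0.23 SD.

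**Step 5: from imbalance to effect estimate.** If follow-up depends on baseline with slope b, a baseline difference δ enters a change contrast as (b − 1)δ. For b between 0 and 1 this is smaller in size than δ. Adjusting for baseline removes it if the relation is linear and drop-out depends only on baseline severity.

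**The case against.** The strongest reply is that the damage is small exactly where the check is weakest. If drop-out is rare, even exactly opposite patterns produce about 0.06 SD, well inside chance imbalance, and a pre-post analysis already uses each child's T1 score. This stands, and it limits how serious the point is.

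It is also fair that a comparison of completers with drop-outs is conventional, and that section 3.1 names no test or threshold. The power figures therefore depend on an assumed test. The variable list is open and could include arm. Adding arm to it would show whether drop-out rates differ, but not which children leave each arm.

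A reader might infer several stronger points that the article does not support:
- *That adjustment will follow only if the check is positive.* The wording says adjustment could be made. That suggests dependence on the check but is no rule.
- *That drop-out is wrongly defined for the waiting list.* The article's primary outcome is change from T1 to T3, and T3 follows the last session, so finishing treatment does track having the T3 value. The definition merely fails to separate a missing T2 from a missing T3.
- *That a bias of about 0.32 SD is to be expected.* That needs 24% loss, which is the recruitment allowance and not a forecast, together with exactly opposite patterns. It is also a baseline imbalance, not a bias in the effect.
- *That missing-data methods have been left out.* A condensed article commonly leaves these to the full protocol or analysis plan.

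What survives is narrower: the article says this comparison can establish whether drop-out is selective, and for a comparison of randomised arms it cannot.

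**Conclusion.** The point holds in a limited form. A completer versus drop-out comparison without regard to arm is insufficient for treatment versus waiting list, and at the drop-out counts the article expects, a null result should not be read as evidence that drop-out is harmless. The power figures rest on the assumed test and the 0.5 SD difference, and the cancellation figures on an illustrative opposite pattern. At 5% to 10% loss the likely effect on the treatment estimate is small. The change is worth making because it is cheap and removes reliance on a weak check, not because a large bias is expected.

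**What to change.** 1. In section 3.1, report drop-out and the baseline profile of drop-outs by allocated arm. Define drop-out per assessment (missing T2, missing T3), so that loss during the first 12 weeks is kept apart from later loss. Present this as description, and remove the statement that it can settle whether drop-out is selective.
2. In section 3.2, include baseline severity and the stratification factors (gender, age group, bilingualism) in the main outcome model for all randomised children, whatever the drop-out comparison shows. State how baseline enters, since T1 should not be both a level of the repeated outcome and a covariate in the same model.

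All of these variables are already collected. The cost is revised wording, a little more analysis and a few degrees of freedom. Neither step addresses drop-out that depends on unobserved outcomes.

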### Intention to treat

3.2

The statistical analyses will be based on the intention-to-treat principle. If appropriate, secondary analyses will be conducted using a per-protocol basis.

Primary and secondary outcomes: Pre-post changes (pretreatment and post treatment assessment of the treatment versus WCG group) on the primary outcome (symptoms of selective mutism) will be tested with repeated measures analyses (factorial repeated measures ANOVA). To determine pre-post change in treatment outcome (responders vs. non-responders) paired sample t-tests will be executed. The effectiveness on secondary outcome measures: symptoms of anxiety/depression, self-image, quality of life and care consumption, will be tested with the same analyses. With linear and logistic regression predictors (e.g., gender, age, socio-economic status, bilingualism, parental psychopathology and parenting styles) for treatment outcome can be determined (p < .05). In the analyses, the number of treatment sessions will be included as a covariate.

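### The pre-post repeated-measures ANOVA is valid but gives away precision: it should adjust for the T1 score and the stratification factors, and by itself it does not deliver the intention-to-treat analysis

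*Protocol article*

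**What the plan says.** Section 3.2 of the protocol article (Intention to treat) defines the primary comparison as "Pre-post changes (pretreatment and post treatment assessment of the treatment versus WCG group) on the primary outcome" and says it "will be tested with repeated measures analyses (factorial repeated measures ANOVA". The same section states: "The statistical analyses will be based on the intention-to-treat principle".

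The only covariate it names is given in the sentence "In the analyses, the number of treatment sessions will be included as a covariate".

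Section 2.1 (Patient recruitment and procedure) says "Randomization will be stratified for gender, age" and adds bilingualism, with age split at up to 7 versus 8 and over. In Section 3.2 gender, age and bilingualism come back only as candidate predictors in separate models: "With linear and logistic regression predictors (e.g., gender, age, socio-economic status, bilingualism, parental psychopathology and parenting styles) for treatment outcome can be determined".

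On drop-out, Section 3.1 calls it rare, sets a recruitment target of 100 to cover it, plans to compare drop-outs with completers, and remarks: "A selective dropout can lead to selection bias, which could be statistically adjusted for".

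The sample-size paragraph arrives at 38 children per group "based on an effect size of d = 0.58 (medium effect size", with two-tailed alpha 0.05 and 80% power, for the T1 to T3 change.

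**The concern.** Three features of the named test deserve attention.

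- **Baseline.** A two-time-point ANOVA uses the T1 score by subtracting it. That is optimal only when T1 and post scores are perfectly correlated. Otherwise regression on T1 removes more noise.
- **Stratification.** Balancing the arms on three factors and then leaving them out of the model keeps their variance in the error term. If they predict change, the standard error is too large and the test is conservative. The Background reports faster treatment progress in younger children, so age is a plausible candidate.
- **Incomplete data.** The classical form of this ANOVA needs a score at every time in the model. A child without the post score contributes nothing, which sits uneasily with an intention-to-treat analysis.

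The first two concern precision and hold even with no missing data. They matter because a trial of 38 per arm has little power to spare.

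**Working it through.** **Inputs from the article.** d = 0.58, two-tailed alpha 0.05, power 0.80, 38 per group (sample-size paragraph); pre and post as the tested times (Section 3.2); recruitment target 100 (Section 3.1). **Assumed:** rho, the correlation between T1 and post scores, from 0.3 to 0.7, with equal SD s at both times.

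**1. The plan's own figure.** n per group = 2(1.960 + 0.842)² / 0.58² = 46.7, so 47 (94 in total). The exact t-test gives 47.6, so 48 (96 in total). At 38 per group the exact two-sided power is 70%. The figure of 38 is reproduced by a one-sided t-test (37.5, rounded up). That discrepancy is a separate matter; here 70% serves only as the starting point.

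**2. Variance.** I read the test of pre-post change between groups as the group-by-time term. With two times its F statistic is the square of the t statistic on change.

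- Change score: 2s²(1 − rho)
- ANCOVA on T1: s²(1 − rho²)
- Ratio ANCOVA/change: (1 − rho)(1 + rho) / [2(1 − rho)] = (1 + rho)/2

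The ratio is below 1 for every rho below 1.

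**3. Power at 38 per arm.** The article does not say which SD the 0.58 refers to, so both scales are shown.

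- d on the post-score SD: effective effect 0.58/√[2(1 − rho)] for change, 0.58/√(1 − rho²) for ANCOVA.
- d on the change SD: 0.58 for change, 0.58 × √[2/(1 + rho)] for ANCOVA.

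| rho | variance ratio | post-score SD: change | post-score SD: ANCOVA | change SD: change | change SD: ANCOVA |
|---|---|---|---|---|---|
| 0.3 | 0.65 | 0.490, 56% | 0.608, 74% | 0.580, 70% | 0.719, 87% |
| 0.5 | 0.75 | 0.580, 70% | 0.670, 82% | 0.580, 70% | 0.670, 82% |
| 0.7 | 0.85 | 0.749, 90% | 0.812, 94% | 0.580, 70% | 0.629, 77% |

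Each cell gives the effective effect and the two-sided noncentral-t power. The one degree of freedom spent on the T1 covariate is ignored. On the post-score scale, the children per arm needed for 80% power are 67 vs 44, 48 vs 36 and 29 vs 25 for change versus ANCOVA.

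**4. Stratification factors.** The article gives no figure for how strongly gender, age group or bilingualism predict change, so no gain can be computed. Only the direction is known: precision is lost if they are prognostic, and none if they are not.

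**5. Incomplete data.** With the target of 100 and d on the change SD, change-score power is 82% without loss and 78% after an assumed 10% loss (45 per arm). I also simulated equal correlations (0.5 and 0.7) with drop-out in the treated arm tied to a high T2 score, at overall losses of about 4% to 13%. The completer estimate stayed between −0.576 and −0.582 against a true −0.58. This is as expected: under equal correlations the covariance of T2 with the T1 to T3 change is rho − rho = 0. Other patterns could produce bias, but the article gives no basis for putting a size on it.

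**The case against.** The best defence is that the named test is valid. Under randomisation the change-score comparison is unbiased, and omitting stratification factors normally errs on the conservative side. The gain from ANCOVA shrinks as rho rises, and rho is unknown. All of this stands, so the point is about efficiency and not about a wrong answer. It does not remove the point, because the article fixes this method and describes no model with T1 or the strata in it.

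A reader might go further and infer that the analysis contradicts intention to treat. The article does not support that. Nowhere does it say that children with missing scores are excluded. Imputation is not ruled out, Section 3.1 leaves room for adjustment, and a statistical analysis plan that is not shown may settle the handling. What remains is that the method alone does not deliver the stated analysis.

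A reader might also infer that one missed assessment of any kind removes a child. The tested times are pre and post, so a missed T2 alone would matter only if T2 were a level of the factor.

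Nor should power after drop-out be worked out from 76, since the target of 100 is there to absorb the loss. Over-recruitment restores numbers but not comparability; with drop-out described as rare, the practical effect may be small.

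**Conclusion.** The point holds as a recoverable loss of precision. The change-score test is unbiased, but its variance exceeds that of ANCOVA by the factor 2/(1 + rho): ANCOVA needs 35% fewer children at rho 0.3 and 15% fewer at rho 0.7. At 38 per arm the power gain is 4 to 18 percentage points if d is on the post-score SD, and 7 to 17 if it is on the change SD. These figures rest on assumed rho, equal SDs at both times and the planned d = 0.58.

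It is tempting to say that ANCOVA restores 80% power at 38 per arm beyond a certain rho. No single threshold can be given. On the post-score scale it needs rho of at least about 0.45; on the change scale it needs rho below about 0.59.

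The loss from omitting the stratification factors has a known direction but no size. The missing-data part is an unresolved tension with intention to treat, not a contradiction.

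**What to change.** In Section 3.2, replace the factorial repeated-measures ANOVA with an ANCOVA or a likelihood-based mixed model on all randomised children, adjusted for the T1 score, gender, age group (as used in the randomisation) and bilingualism.

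State how children without the post score enter. A mixed model that treats T1 as a response with a common mean in both arms keeps every child with a T1 score, under a missing-at-random assumption. An ANCOVA needs imputation to do the same. Keep the drop-out versus completer comparison as description only.

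This point does not settle whether the primary contrast is at T2 or T3; that is a separate question, and the model serves either.

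The cost is wording. The T1 scores are already scheduled, and the three factors must be known before a child can be randomised.

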
## Methods/design

2

***Design:*** this study is a single-center, single-blinded randomized controlled trial (RCT), comparing protocolized behavioral therapy for selective mutism to a waiting list control group.

***Inclusion:*** eligible are children between the age of 3–18 years old, with an estimated IQ of 85 or higher, who understand Dutch and are referred to our academic center for diagnosis and treatment of selective mutism between September 2018 and March 2020. This large age span covers all consecutive patients referred to our institution. Though the vast majority of these children is under the age of 8, we also get referrals up to 18 years.

***Exclusio******n******:*** ineligible are children who have primary diagnoses other than selective mutism. Comorbidity is not excluded, but the primary and most impairing diagnosis has to be selective mutism. During the intake, it will be assessed what the most urgent need for help is and what type of care is most indicated. In the case that treatment is indicated for a comorbid diagnosis at first, the child will be excluded from the study.

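### The only test named for response is a paired t-test, which does not compare the randomised arms, so it cannot support a treatment effect on response

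*Protocol article*

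**What the plan says.** The design in section 2 (Methods/design) is a randomised trial "comparing protocolized behavioral therapy for selective mutism to a waiting list control group". Section 2.1 (Patient recruitment and procedure) sets the allocation: "children are randomly assigned to treatment for selective mutism (N = 38) or the waiting list control group (WCG: N = 38".

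Section 3.2 (Intention to treat) names three kinds of analysis:

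- **Symptom score.** Pre-post change, treatment versus waiting list, "will be tested with repeated measures analyses (factorial repeated measures ANOVA"). This compares the arms.
- **Response.** "To determine pre-post change in treatment outcome (responders vs. non-responders) paired sample t-tests will be executed". No arm term and no between-arm test is named.
- **Predictors.** "With linear and logistic regression predictors (e.g., gender, age, socio-economic status, bilingualism, parental psychopathology and parenting styles) for treatment outcome can be determined". This is the only method named that suits a binary outcome. Its purpose is prediction, and arm is not among the examples listed.

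The secondary outcomes (anxiety/depression symptoms, self-image, quality of life, care consumption) "will be tested with the same analyses".

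**The concern.** A paired t-test asks whether a mean moved within one set of children. Response as a treatment effect is a different question: is the proportion of responders higher in the treated arm than in the waiting-list arm? The stated method does not answer it.

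What is at stake is how a response result would be interpreted. Symptoms may ease over the study period for reasons unrelated to therapy, such as maturation, adjustment to school or regression to the mean. The waiting list is there to remove such change. A within-arm test leaves it in, so a significant result could be reported as response to treatment when both arms improved equally. Response is an easily understood result, and section 4.2 (Implications for clinical practice) foresees wide roll-out, so this result should rest on the randomisation.

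**Working it through.** **1. The plan's own figure.** The article gives no sample size, response rate or background improvement for response. Its calculation, "based on an effect size of d = 0.58 (medium effect size), an alpha of 0.05 (two-tailed) and a power of 0.8", leading to "a sample size of 76 (38 per group) is needed", concerns T1-T3 change in symptoms. It enters here only as the source of n = 38 per arm. Whether 76 follows from those inputs is a separate question and does not bear on this point.

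**2. Three readings of the response sentence.**

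| Reading | What is tested | Are the arms compared? | Further problem |
|---|---|---|---|
| A | 0/1 status, before and after, within an arm | No | A t-test does not suit the variable |
| B | Scores, before and after, within responders and within non-responders | No | Probably circular: response would normally be defined from the same change that is then tested |
| C | Scores, before and after, within each arm | No | The control arm is not used as a comparator |

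The readings differ in what else goes wrong. They agree that the arms are not compared.

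**3. Size under reading C.** Inputs: n = 38 (section 2.1) and two-sided alpha 0.05 (sample size paragraph). Assumed: pre-post correlation r = 0.5, background improvement g in SD units, no treatment effect. The standardised paired difference is dz = g / √(2(1 − r)). At r = 0.5 the denominator is √1 = 1, so dz = g. Power of the one-sample t-test on differences, 37 degrees of freedom:

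| g (assumed) | Probability of p < 0.05 |
|---|---|
| 0.1 SD | 9% |
| 0.2 SD | 22% |
| 0.3 SD | 44% |
| 0.4 SD | 67% |
| 0.5 SD | 85% |

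For r between 0.3 and 0.7 the range is 33% to 64% at 0.3 SD and 72% to 97% at 0.5 SD.

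**4. Size under reading A.** Assume that all 38 children are non-responders at T1 and that k respond later. The differences are k ones and 38 − k zeros, with mean p = k/38 and standard error √(p(1 − p)/37).

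- k = 3: p = 0.079, SE = 0.0443, t = 1.78, below the critical value of 2.03.
- k = 4: p = 0.105, SE = 0.0505, t = 2.09, two-sided p-value 0.044.

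Four responders of 38 are therefore enough. If the true rate is the same in both arms, the treated arm is significant with probability P(X ≥ 4), X ~ Binomial(38, rate):

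| Common response rate (assumed) | Within-arm paired t-test | Between-arm chi-square test |
|---|---|---|
| 5% | 0.12 | 0.041 |
| 10% | 0.54 | 0.058 |
| 20% | 0.96 | 0.050 |
| 30% | 0.999 | 0.052 |

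**5. What a between-arm comparison could detect.** With 38 per arm and two-sided 0.05, power is 0.83 for 5% versus 30%, 0.87 for 10% versus 40%, 0.80 for 20% versus 50%, and 0.48 for 20% versus 40%, which would need 82 per arm. All rates are assumed. At 5% versus 30%, the expected number of responders is 38 × (0.05 + 0.30) ≈ 13. That is few for a model with arm, T1 severity and three stratification factors (five terms).

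**The case against.** A reader might infer that the trial's effectiveness claim as a whole ignores the control group. The article does not support that. The sentence before the one on response compares treatment with waiting list on the primary symptom outcome by ANOVA, and the reference to the same analyses carries that ANOVA to the secondary outcomes too. Response is not listed as an outcome in Table 1 and is not the basis of the sample size. This objection stands and limits the point to response, and to any secondary outcome for which the paired t-test is also carried over.

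The sentence is also ambiguous. It may describe within-group change only, or subgroups that feed the predictor aim, and it does not say that a binary variable will be t-tested. That stands as well: no single misuse can be asserted. But paired t-tests are the only method named for response, and no reading supplies a between-arm comparison.

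A reader might take the percentages above as type I error rates. They are not. A paired t-test that detects a real background change is correct for its own null hypothesis; the error lies in attributing that change to treatment, and section 3.2 does not say this will be done. The assumed improvements also have no source in the article, which says in the Background that untreated selective mutism can be chronic. Section 2 sets no severity threshold for entry, so regression to the mean is possible but not shown. If background change is small, the distortion on scores is small too (9% at 0.1 SD).

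Finally, the missing definition of a responder is not a fault here, since a condensed article may leave it to the full protocol or SAP.

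**Conclusion.** The point holds for response. The stated method cannot support a treatment effect on response under any reading, and nothing else in the article supplies the missing comparison. This is a method stated in the article, not a detail deferred to a later document. The symptom-score analysis does compare the arms and is not in question here.

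The size cannot be fixed from the article. Over the assumed ranges, a within-arm test with no treatment effect would be significant in 9% to 85% of trials on scores (0.1 to 0.5 SD, r = 0.5, n = 38). On 0/1 status the probability is 0.12 to 0.999 (common rates of 5% to 30%, no responders at T1). These figures matter only if the change is presented as an effect of treatment. Should-fix.

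**What to change.** Replace the response sentence in section 3.2 with a between-arm comparison of the responder proportion at T2, analysed as randomised. T2 is the assessment at which waiting-list children have only waited; section 2.3 says that both groups receive the treatment protocol, and T3 follows the last session. Derive status from the ADIS-C selective mutism section or the SMQ, both collected at T2 according to Table 1. Report the risk difference with 95% CI. Adjust for T1 severity and the stratification factors (gender, age group, bilingualism) only if the number of events allows; otherwise a simple comparison of proportions is enough.

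Label within-group paired changes, including T1-T3, as descriptive. State whether the paired t-test is meant to apply to the secondary outcomes; if so, give it the same label there.

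The cost is wording only, with no new data or visits. The downside is precision. T2 falls at 12 weeks and average treatment lasts 22 weeks (section 2.2), so many children will be mid-treatment. Response may be infrequent and the estimate imprecise, and the write-up should say so.
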